## Abstract

**Background:**

Scientific evidence for the frequency of monitoring of type 2 diabetes patients is lacking. If three-monthly control in general practice could be reduced to six-monthly control in some patients, this would on the one hand reduce the use of medical services including involvement of practice nurses, and thus reduce costs, and on the other hand alleviate the burden of people with type 2 diabetes. The goal of this study is to make primary diabetes care as efficient as possible for patients and health care providers. Therefore, we want to determine whether six-monthly monitoring of well-controlled type 2 diabetes patients in primary care leads to equivalent cardiometabolic control compared to the generally recommended three-monthly monitoring.

**Methods and design:**

The study is a randomised controlled patient-preference equivalence trial. Participants are asked if they prefer three-monthly (usual care) or six-monthly diabetes monitoring. If they do not have a preference, they are randomised to a three-monthly or six-monthly monitoring group. Patients are eligible for the study if they are between 40 and 80 years old, diagnosed with type 2 diabetes more than one year ago, treated by a general practitioner, not on insulin treatment, and with HbA1c ≤7.5%, systolic blood pressure ≤145 mmHg and total cholesterol ≤5.2 mmol/l. The intervention group (six-monthly monitoring) will receive the same treatment with the same treatment targets as the control group (three-monthly monitoring). The intervention period will last one and a half year. After the intervention, the three-monthly and six-monthly monitoring groups are compared on equivalence of cardiometabolic control. Secondary outcome measures are HbA1c, blood pressure, cholesterol level, Body Mass Index, smoking behaviour, physical activity, loss of work due to illness, health status, diabetes-specific distress, satisfaction with treatment and adherence to medications. We will use intention-to-treat analysis with repeated measures. For outcomes that have only baseline and final measurements, we will use ANCOVA. Depending on the results, a cost-minimisation analysis or an incremental cost-effectiveness analysis will be done.

**Discussion:**

This study will provide valuable information on the most efficient control frequency of well-controlled type 2 diabetes patients in primary care.

**Trial registration:**

Current Controlled Trials ISRCTN93201802

## Background

At the end of 2007 more than 660.000 people were diagnosed with type 2 diabetes in the Netherlands [1]. The number of type 2 diabetes patients is still increasing [1], and also their use of health care facilities. Furthermore, the overall workload of general practitioners is increasing [2]. The current guideline on type 2 diabetes in primary care in the Netherlands advises to monitor type 2 diabetes patients four times a year [3], but this advice is not evidence-based. Three quarterly controls are done by the practice nurse and the general practitioner is advised to perform the annual check-up. Comparing 15 diabetes guidelines in 13 countries, the advised frequency of monitoring HbA1c ranged from one to four times a year and monitoring blood pressure ranged from one to six times a year [4]. It is obvious that the workload for healthcare professionals will differ significantly, depending on the guideline that is followed.

A retrospective, observational study in Spain demonstrated that the improvement in glycaemic control over time in patients with type 2 diabetes in general practice was not related to the number of visits to the general practitioner, but to changes in treatment [5]. More evidence on the desired frequency of type 2 diabetes controls in general practice is lacking.

A randomised equivalence trial in Canada compared blood pressure control, adherence to treatment and patient satisfaction in patients with treated hypertension followed up by their family physicians every three or six months. Patients with follow-up every three months achieved the same levels of blood pressure control, adherence to treatment and patient satisfaction compared to patients with follow-up every six months [6].

If, in accordance with the hypertension example, the contact time with the diabetes team in well-controlled type 2 diabetes patients could also be reduced up to 50% without deteriorating their quality of care, this could reduce the patient burden as well as induce savings on direct medical costs and relieve the workload of practice nurses.

Therefore we designed the EFFIcient MOnitoring of DIabetes (EFFIMODI) study, aiming to make primary diabetes care as efficient as possible for patients and health care providers. We hypothesise that six-monthly monitoring of well-controlled patients with type 2 diabetes in primary care results in equivalent cardiometabolic control as the currently recommended three-monthly monitoring, with less costs.

## Methods and design

### Study design

The study has been designed as a randomised controlled patient-preference equivalence trial. In practice this design means that participants are asked if they prefer three-monthly (usual care) or six-monthly diabetes monitoring. If they do not have a preference, they are randomised to a three-monthly or six-monthly monitoring group. This will result into four study groups (see Figure 1).

**Figure 1 F1:**
[figure not shown]
**Participant flowchart**. The participant flowchart with the expected number of patients, based on a small survey.

We chose to conduct a patient-preference trial because of two reasons [7]. First, it gives us the possibility to compare the relationship between patients' preference for a frequency of diabetes control and the study outcomes. Second, more people will participate in the study, as people can choose not to be randomised; they can be included in the so-called 'observational' study arm of their choice. Doing so, we will have information about people who are not randomised and this will help in generalising the results. In conducting a patient-preference trial we will avoid selection and probably also drop-out after randomisation.

We chose to conduct an equivalence trial, because we want to assess whether six-monthly monitoring results in equal cardiometabolic control compared to the current frequency of control [8]. Since we expect that six-monthly monitoring will not give better cardiometabolic control than three-monthly monitoring, we did not choose a non-inferiority trial. The intervention period will last one and a half year, so patients will be seen either seven or four times during the intervention period.

The Medical Research Ethics Committee of the University Medical Center Utrecht has approved the study protocol (Protocol number: 08-453).

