### Sample size calculation

The sample size is calculated on the assumption of equivalence of cardiometabolic control. Therefore, we used the formula from Jones et al. [8]: n = (2p(100-p)*(Z_(1-α)_+Z_(1-β)_)^2^)/δ^2^, where p is the overall percentage of successes to be expected if the treatments are equivalent, δ indicates the range of equivalence for the difference in percentage success rates, α is the probability of type I error and β the probability of type II error.

We assume equivalence if the two-sided 95% confidence interval (α = 0.05; Z_(1-α) _= 1.96) for the difference in cardiometabolic control between the two intervention groups is completely in the range from -5 to 5% (δ = 5). With a supposed overall percentage of success of 95% and a power of 90% (β = 0.1; Z_(1-β) _= 1.28), we need a sample size of 399 people per randomised group. Based on a small survey that was performed by the Julius Center, we assume that ~50% of the people have no preference and thus will be randomised. About the other half of the people is assumed to have a strong preference for the frequency of monitoring. Therefore, we need to include 1596 patients: 798 in the randomised arms and 798 in the observational arms.

As said earlier in the **study population **section, we assume that 20% of the type 2 diabetes patients will fulfil the inclusion criteria. With an average of 80 type 2 diabetes patients per practice, we expect that sixteen patients in each general practice will meet the eligibility criteria. Taking into account a response rate of 60%, ten patients in each practice will be willing to participate in the study: five in the observational arm and five in the randomised arm, so at least 160 general practitioners will have to be recruited. As people may drop out during the study, we will recruit 1800 patients allowing an 11% drop-out; therefore we need 180 general practitioners. Figure 1 shows the participant flowchart with the expected numbers.

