#### Economic evaluation

Should this study demonstrate equivalent outcomes with different frequencies of diabetes monitoring, the evident cost-reduction of less control visits merit the conclusion that six-monthly monitoring is the approach of first choice and a cost-minimisation analysis will be done. This is likely to provide sufficient evidence to change the frequency of monitoring in well-controlled type 2 diabetes patients in general practice.

However, should the three-monthly follow-up scheme result in a better cardiometabolic control, a cost-effectiveness analysis will be performed. If better outcomes can be realised with a higher control frequency at an associated higher cost to society, or vice versa, (somewhat) worse patient outcomes at a lower cost, the balance between costs and outcomes is of interest. Differences in the number of QALYs between groups during the study period will be assessed. The difference in treatment effect will be calculated as follows: for each group the difference between baseline and final measurements in percentage of patients with good cardiometabolic control will be determined. The absolute difference between measurements pre- and post-intervention will be taken as the intervention effect. Accordingly, differences in QALYs between groups will be calculated. The 'incremental cost-effectiveness ratio' (ICER) will be expressed as cost differences between groups divided by differences in treatment effects between groups. Confidence intervals will be determined using bootstrapping [19]. A 'cost-effectiveness acceptability curve' (CEAC) will also be drawn using the bootstrap sample. Cost-utility estimates will be derived accordingly, using QALY differences between groups as outcome measure.

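### The reason given for rejecting non-inferiority is inverted, and the stated 90% power belongs to that rejected design: the ±5-point equivalence rule has 80% at 399 per group

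*Protocol article*

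**What the plan says.** All places are in the protocol article.

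- **Study design (text after Figure 1)** gives two reasons for the design. The positive one is: "We chose to conduct an equivalence trial, because we want to assess whether six-monthly monitoring results in equal cardiometabolic control". The reason for not using the alternative is: "Since we expect that six-monthly monitoring will not give better cardiometabolic control than three-monthly monitoring, we did not choose a non-inferiority trial".
- **Sample size calculation** sets the success rule: "We assume equivalence if the two-sided 95% confidence interval" for the difference in cardiometabolic control "is completely in the range from -5 to 5% (δ = 5"). The inputs are "α = 0.05; Z_(1-α) _= 1.96", then "With a supposed overall percentage of success of 95% and a power of 90" per cent, with "β = 0.1; Z_(1-β) _= 1.28". The result is 399 per randomised group.
- **Analysis, Economic evaluation** says that equivalent outcomes, with the saving from fewer visits, would "merit the conclusion that six-monthly monitoring is the approach of first choice" and lead to a cost-minimisation analysis. If three-monthly monitoring gives better control, a cost-effectiveness analysis follows. The Discussion names the same two results. Neither section has a branch for six-monthly monitoring being better.

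**The concern.** Non-inferiority asks only whether the new schedule is worse by more than the margin. It carries no expectation that the new schedule is better. If six-monthly monitoring is expected to be no better, the limit that matters is the lower one (six-monthly minus three-monthly, -5 points). The quoted expectation therefore argues for the design it is used to reject.

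The Background asks whether contact time can be cut without loss of quality, and the planned consequences follow only from equivalence or from three-monthly being better. No stated decision needs protection from six-monthly being more than 5 points better. Yet a confidence interval that crosses +5 stops the trial from declaring equivalence.

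The sample size compounds this. The rule has two limits, but the calculation allows for failure at only one. The trial could then end without showing equivalence more often than its stated 90% power implies.

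**Working it through.** **Inputs** (Sample size calculation): success p = 95% in both groups, so true difference 0; δ = 5 points; 1.96 for the two-sided 95% interval; 1.28 for β = 0.1.

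**1. Reproduce the plan's figure.** n = 2p(100-p)(1.96+1.28)²/δ² = 2 × 95 × 5 × 3.24²/25 = 398.9, so 399 per group. The figure is reproduced.

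**2. Power of the lower limit alone at n = 399.**
- SE = √(2 × 95 × 5/399) = 1.543 points.
- δ/SE = 5/1.543 = 3.24, and 3.24 - 1.96 = 1.28.
- Power = Φ(1.28) = 0.90.

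The stated 90% is thus the chance that the lower limit lies above -5.

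**3. Power of the stated rule.** At zero difference each limit fails with probability 0.10, and both limits cannot fail together here, because the interval's half-width (1.96 × 1.543 = 3.02 points) is below 5. Power = 1 - 2 × 0.10 = 0.80. A simulation of 400,000 trials gave 89.7% for the lower limit alone and 79.4% for both limits.

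**4. Sample size for 90% under the stated rule.** Replace 1.28 by Z(1-β/2) = 1.645: 38 × (1.960+1.645)² = 493.8, so 494 per group (988 randomised, against 798).

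**5. Which results fail only at the upper limit?** With half-width 3.02 points, the interval crosses +5 when the estimate exceeds 5 - 3.02, about +2 points. Those results all favour six-monthly monitoring.

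**6. Dependence on the true difference** (n = 399 per group, three-monthly fixed at 95%, unpooled normal approximation):

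| Six-monthly success | Lower limit only | Both limits | Cost of upper limit (points) |
|---|---|---|---|
| 95% | 90.0% | 80.0% | 10.0 |
| 94.5% | 81.3% | 74.9% | 6.4 |
| 94% | 69.8% | 65.9% | 3.9 |
| 93% | 43.1% | 41.7% | 1.4 |

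Over the range that the protocol expects (six-monthly no better), the cost is largest at zero difference. It would be larger still if six-monthly were truly better (96% against 95%: 98.3% against 76.2%).

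**7. Recruitment target.** If all 1800 recruits stayed, with half randomised, there would be 450 per group. Power would be 93.1% for the lower limit and 86.2% for both.

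**The case against.** The strongest reply is that equivalence does not rest on the faulty sentence. The sentence before it states the aim of showing equal control, and the hypothesis in the Background matches. Equivalence is also the stricter claim: an interval inside ±5 shows non-inferiority at the same margin and level, so the rule cannot produce a false claim for six-monthly monitoring that non-inferiority would have avoided. Cost-minimisation also fits a finding of equal effects better than one of not being worse by 5 points. All of this stands. A reader might infer that the equivalence design is invalid, or that the trial must change to non-inferiority. The documents do not support that.

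A reader might also infer that the upper limit always costs 10 points and makes up half of the false-negative risk. That holds only at zero true difference with 399 analysed. At 94% against 95%, the upper limit accounts for 3.9 of the 34.1 points of risk, about 11%.

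Nor should the gap be enlarged by assuming lower success rates. The protocol plans only for 95%. At 90% in both groups, for example, power would be 65% for the lower limit and 31% for both, so most of the fall comes from the rate itself, and changing the rule would not restore 90%.

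Finally, the shortfall can equally be described as a formula error: the one-limit term Z(1-β) was used with a two-limit rule. That is correct, and it is why there are two valid repairs. It does not rescue the quoted sentence or the stated power.

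**Conclusion.** The point holds in two linked parts. First, the reason for rejecting non-inferiority is inverted and should go; the separate aim of showing equal control can support equivalence without it. Second, rule, sample size and power do not agree. With 95% success in both groups, zero true difference and 399 analysed per group, the rule as written has 80% power, not 90%. The 80% assumes the normal approximation, which simulation supports. The 10-point shortfall is measured at the protocol's own planning assumption, and the part due to the upper limit falls to about 4 points or less once six-monthly success is a point or more lower. Even with 450 per group and no drop-out, the two-limit rule stays below 90%.

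**What to change.** Before outcome data are seen, delete the sentence in Study design that rejects non-inferiority, and adopt one of two repairs.

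**(a) Non-inferiority as the primary criterion.** Success if the lower limit of the same two-sided 95% interval (six- minus three-monthly) is above -5 points. Margin, interval and 399 per group stay, and the stated 90% becomes true. Report ±5 equivalence as supportive, and reword the trigger for cost-minimisation in the Economic evaluation to match. No extra patients or data are needed. The cost is a weaker claim (not worse by 5 points or more) and an amendment to the primary hypothesis of an ethics-approved, registered trial, carried through every section that states equivalence.

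**(b) Keep two-sided equivalence.** Justify it only by the aim of showing equal control, and restate power as about 80% at 399 per group. The cost is a less favourable stated power. Keeping 90% would need about 494 per group: 95 more per group, 190 more randomised and, with half of participants having no preference, 380 more in all (1976 against 1596) before drop-out.

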### Study population

Patients are eligible for the study if they are between 40 and 80 years old, diagnosed with type 2 diabetes for more than a year, treated by their general practitioner, not on insulin treatment and overall well-controlled, defined as having HbA1c ≤7.5% and systolic blood pressure ≤145 mmHg and total cholesterol ≤5.2 mmol/l. These HbA1c, systolic blood pressure and total cholesterol values are a little higher than the Dutch target values (HbA1c ≤7.0%, systolic blood pressure ≤140 mmHg and total cholesterol ≤4.5 mmol/l [3]). We decided to choose more liberal values to create a larger target population to be randomised. According to the stricter target values only 18.9% of all type 2 diabetes patients fulfilled these values [9]. Because of the minimal difference with the target values, we assume that 20% of the type 2 diabetes patients will fulfil the inclusion criteria.

### Recruitment of practices and patients

We will approach the boards of several health care groups to recruit general practitioners. These health care groups have a central database in which all type 2 diabetes patients are recorded. In this database all determinants that are needed for the selection of study patients are included (see **study population **for the inclusion criteria). The health care groups will ask all their affiliated general practitioners to participate in the study. If a general practitioner wants to participate he will obtain the selection of patients, according to the inclusion criteria, from the health care group. The general practitioner sends an information letter as well as an informed consent form to the selected patients.

Patients who want to participate have to fill in the informed consent form. The participants are asked whether they strongly prefer three-monthly (current care) or six-monthly diabetes control or whether they have no preference. Patients with a preference will enter the 'observational arm'. If participants do not have a strong preference for the frequency of care, they will be randomised.

### Randomisation and blinding

Participants without a preference for either three-monthly or six-monthly monitoring are randomised into one of the two randomised study arms in a 1:1 ratio: a control group that will receive current care, comprising diabetes control once per three months, and an intervention group that will receive diabetes control once per six months. In both randomised groups the extensive annual check-up will be done by the general practitioner. The treatment targets, therapeutic algorithms and life style advices will remain unchanged and do not differ between the intervention and control groups.

Randomisation is generated at the patient level by a computerised random-number generator at the Julius Center. Participants are randomised before baseline data are collected. Since this is a pragmatic trial, it is not necessary to blind participants and general practitioners for the treatment allocation. However, the laboratory technicians who measure HbA1c and cholesterol are not aware of study participation of the patients.

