#### Medical records

Biomarkers (HbA1c, cholesterol, fasting blood glucose) and anthropometric variables (blood pressure, Body Mass Index) will be collected from the general practitioners' computerised information system. Information on the most recently measurements of the biomarkers and anthropometric variables before the study, medical history, medication use before the study and all measurements performed during the first EFFIMODI visit will be collected just after the start of the study. All measurements during the follow-up period will be collected after the end of the follow-up period. The same applies to the number of diabetes and non-diabetes related visits to the general practitioner and (differences in) medication use during the study.

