#### Questionnaires

The participants will be asked to complete an extensive questionnaire before (t = 0) and after (t = 18 months) the intervention period. This questionnaire comprises general background information on age, gender, ethnicity, education, smoking, physical activity, occupation and loss of work due to illness, health status, diabetes-specific distress and satisfaction with diabetes treatment.

Current smoking is measured as the number of cigarettes per day or the number of cigars per week. Smoking in the past is measured the same way. Also the number of pack years is recorded. Physical activity is measured with the Short Questionnaire to Assess Health-enhancing physical activity (SQUASH) [10]. The SQUASH is a reliable and valid questionnaire to measure the level of physical activity in an adult population. The questionnaire was designed to give an indication of the habitual activity level. Information on light (range: 2-4 Metabolic Equivalent of Task (MET)), moderate (range: 4-6.5 MET) and vigorous (>6.5 MET) intensity physical activities will be obtained. Physical activity will be expressed in minutes per week and in a total activity score. The total activity score will be calculated by multiplying the minutes per week by the actual MET score of the specific activity (MET/min/week).

Occupation and loss of work due to illness are measured with the Short Form Health and Labour Questionnaire (SF-HLQ) [11]. The SF-HLQ consists of three parts: absenteeism from paid work, production losses without absenteeism from paid work and hindrance in the performance of paid and unpaid work. Data derived with this questionnaire will be used to calculate costs of productivity losses, should incremental cost-effectiveness be merited at closure of the trial (see **economic evaluation**).

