### Analysis

We will use repeated measures analysis for all recorded measurements of HbA1c, blood pressure, cholesterol and fasting blood glucose to optimally use all available data. Data from the questionnaires at the start and at the end of the intervention period will be analysed using ANCOVA. Data will be analysed according to intention-to-treat. For handling missing data we will use multiple imputation [18]. After the intervention, the randomised three-monthly and six-monthly monitoring groups are compared on equivalence of cardiometabolic control.

Since this trial is a patient preference trial, we will also compare the three-monthly preference group with the three-monthly randomised group. Depending on the number of patients opting for the six-monthly controls, we will compare this group with the six-monthly randomised group. In these analyses, we will examine determinants of preference, and we will determine risk profiles of patients. This will facilitate the applicability of the results and we can demonstrate if people who are more motivated will have better cardiometabolic control. Figure 2 provides an overview of all comparisons that will be made between the groups.

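### The questionnaire baseline is taken after open randomisation and then serves as the implied ANCOVA covariate, which puts the patient-reported effects and any QALY change at risk of bias

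*Protocol article*

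**What the plan says.** Randomisation and blinding (protocol article) fixes the order: "Participants are randomised before baseline data are collected". The same paragraph says that "it is not necessary to blind participants and general practitioners for the treatment allocation", on the ground that the trial is pragmatic. The one masking measure is that "the laboratory technicians who measure HbA1c and cholesterol are not aware of study participation of the patients".

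Under Questionnaires, patients are asked to "complete an extensive questionnaire before (t = 0) and after (t = 18 months) the intervention period". This instrument carries the SF-36, EQ-5D, PAID, DTSQ, SQUASH and the work-loss items. The Analysis section says: "Data from the questionnaires at the start and at the end of the intervention period will be analysed using ANCOVA". The abstract gives the general rule: "For outcomes that have only baseline and final measurements, we will use ANCOVA". That the t = 0 score is the covariate is implied by the method and not written out.

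The Economic evaluation text under Analysis takes the difference between pre- and post-intervention values as the intervention effect and says that QALY differences follow in the same way. The EQ-5D from t = 0 is the only starting value for that.

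For the primary outcome, the Analysis section says: "After the intervention, the randomised three-monthly and six-monthly monitoring groups are compared on equivalence of cardiometabolic control". It names no baseline covariate.

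**The concern.** ANCOVA gives an unbiased treatment effect in a randomised trial because the covariate cannot depend on the allocation. A score collected after an open allocation loses that guarantee. The allocation here is how often the patient will be seen. Satisfaction with treatment and diabetes distress are measures that could move when a patient hears the answer.

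Two errors are possible. If the reaction is short-lived and gone by 18 months, adjusting for it creates a difference between arms that does not exist. If it lasts, adjusting for it removes part of a genuine effect and pulls the result towards no difference. The second case matters because relieving patient burden is one of the trial's stated aims, and these questionnaires measure it.

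An analysis plan that is not shown could add a sensitivity analysis, but it could not turn a questionnaire completed after randomisation into one completed before it.

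**Working it through.** **Inputs from the document.** Randomisation precedes baseline, allocation is open, questionnaires are at 0 and 18 months, and the method is ANCOVA. The arm size of 399 comes from the Sample size calculation section and reproduces: 2 × 95 × 5 × (1.96 + 1.28)² / 5² = 398.9, rounded up to 399. The point made here does not change that number; it is used only to set the standard error.

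**Inputs assumed, because the document gives none.** The shift d in the baseline score of one arm is taken as 0.1, 0.2 or 0.3 SD. The correlation r between baseline and final score is taken as 0.5 or 0.7. With equal variances, the ANCOVA slope b equals r in SD units.

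**Transient shift, true effect zero.** The final means are equal and the baseline means differ by d.
- ANCOVA effect = 0 - b × d = -b × d
- Change-score effect = 0 - d = -d
- SE of the ANCOVA effect ≈ √[(1 - r²) × (2/399 + d²/798)]
- Type I error = P(|Z + r × d/SE| > 1.96)

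For r = 0.5 and d = 0.1, the SE is √[0.75 × (0.005013 + 0.000013)] = 0.0614, the ratio is 0.05/0.0614 = 0.81, and the type I error is 12.9%.

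| r | d (SD) | ANCOVA bias (SD) | Change-score bias (SD) | ANCOVA type I error |
|---|---|---|---|---|
| 0.5 | 0.1 | -0.05 | -0.1 | 13% |
| 0.5 | 0.2 | -0.10 | -0.2 | 37% |
| 0.5 | 0.3 | -0.15 | -0.3 | 68% |
| 0.7 | 0.1 | -0.07 | -0.1 | 28% |
| 0.7 | 0.2 | -0.14 | -0.2 | 79% |
| 0.7 | 0.3 | -0.21 | -0.3 | 98% |

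A simulation with 399 per arm and 1,500 runs per setting agrees: 12%, 37% and 65% at r = 0.5, and 29%, 79% and 99% at r = 0.7. With d = 0, or with the post-randomisation covariate left out, the rate stays near 5%.

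**Lasting shift.** If the reaction is genuine and the final means also differ by d, ANCOVA returns d - b × d = (1 - b) × d. That is half of the effect at b = 0.5 and 30% of it at b = 0.7. A change score returns d - d = 0.

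**Primary outcome.** The contrast is the difference in final percentages. No baseline term enters it, so the timing of baseline contributes no bias.

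**Optional adjustment of the primary outcome.** Pre-study HbA1c, blood pressure and cholesterol are collected from the records (Medical records section). In simulation at the planned 95% success, with assumed correlations of 0.5 to 0.8, adjusting for the three pre-study values reduced the variance of the risk difference by about 1.5% to 5%. The unadjusted 95% half-width is 1.96 × √(2 × 0.95 × 0.05/399) = 3.02 percentage points. A 5% variance reduction narrows it by 3.02 × (1 - √0.95) = 0.08 point, against a margin of 5.

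**The case against.** The article does not say that patients had been told their arm when they filled in the t = 0 questionnaire, and it places that questionnaire before the intervention period. If allocation was still undisclosed, d is zero and nothing follows. Only patients without a strong preference are randomised, and they are the ones least likely to react to the result. Some items, such as habitual physical activity or the frequency of hyperglycaemia over recent weeks, are unlikely to move on hearing a visit schedule. These arguments stand: they limit the likely size of d and rule out calling the bias shown. They do not remove the risk, because the design is open, the order is explicit, and no safeguard against early disclosure is described.

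Two stronger readings are tempting, and the document supports neither.

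- **That the primary analysis is compromised, or defective for want of baseline adjustment.** The planned comparison uses final values only. HbA1c and cholesterol are measured by technicians unaware of study participation; blood pressure lacks that protection, but this is not a matter of baseline timing. The choice of covariates is commonly left to an analysis plan, and the gain here is small.
- **That the last pre-study record values should become the baseline for the cost-effectiveness change in percentage controlled.** Eligibility requires all three limits to be met. If the pre-study values are those used for selection, about 100% are controlled at baseline in both arms by construction, so the change adds nothing to the final percentage, and each arm's decline includes regression to the mean.

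**Conclusion.** The point holds for the secondary patient-reported outcomes and for QALYs built on the t = 0 EQ-5D. The protocol fixes an order in which the implied ANCOVA covariate is a subjective score taken after open allocation, and nothing elsewhere in the article repairs it.

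The size is conditional. Over the assumed ranges the ANCOVA bias runs from -0.05 to -0.21 SD, and even the smallest assumed shift more than doubles the nominal 5% error rate. A shift of zero leaves no bias. All of this rests on patients knowing their arm at t = 0 and on assumed values of r and d, so it is a risk and not a finding of bias. The QALY consequence is further limited because that analysis is planned only if three-monthly monitoring gives better control. The sample size and the primary equivalence conclusion are untouched.

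**What to change.** Collect the t = 0 questionnaire after consent and before randomisation. If that is not feasible, release the allocation only once the questionnaire has been returned, and say so under Randomisation and blinding. State in the Analysis section that the ANCOVA covariate is this pre-allocation score, and use the same EQ-5D value for any QALY change.

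If the order cannot be changed, pre-specify a sensitivity analysis of the questionnaire outcomes that omits the post-randomisation baseline covariate, and record whether each patient knew the allocation when completing t = 0.

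The cost is a short delay between consent and allocation. Mailing an extensive questionnaire together with the consent form might lower the assumed 60% response; sending it after consent avoids that. No new measurement and no change in sample size are needed.

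Optionally, adjust the primary risk difference for pre-study HbA1c, systolic pressure and total cholesterol, for the small gain in precision shown above.
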